### Trial design

The study is designed as a non-randomised, single-arm longitudinal observational study with repeated measurement points in the context of health services research. It is conducted from January 2023 to June 2025, spanning a total duration of 30 months and comprising five phases. The first one, the preparatory phase focused on the requirements of implementation. These were assessed by participating GPs and selected according to the following criteria: (1) village where home visits are carried out (2), number of patients receiving home visits, and (3) share suitable for visiting a VaO room. Suitable premises were selected in collaboration with local mayors. A checklist in accordance with the Association of General Practitioners in Germany (VirchowBund) was used to ensure alignment of the facilities [15]. The criteria included, for example, accessibility, sanitary facilities and stable internet connections. The rooms were inspected by HPs and GPs.

In the initial assessment and testing phase, patients’ care in VaO rooms by their known HPs starts. The HPs continuously monitor the patients’ state of health to determine their suitability for care in VaO rooms [16]. The subsequent interim evaluation and concept adjustment phase aims to correct weaknesses, sources of risk and errors from the initial assessment and testing phase by conducting a focus group interview with the participating HPs on their satisfaction with the use of the room. Sources of risk and errors are targeted while adjustments to the VaO concept optimise processes. In the second survey phase, the time and distance parameters of patient care are continuously collected. A final evaluation is carried out at the end of the study to test the hypotheses.

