### Patient recruitment

Patients are recruited directly by the participating GPs. Patients who meet the following inclusion criteria are contacted directly by their GPs and provided with further information about the study. The final date for patient enrolment is December 31, 2024. Data on travel time, setup time and distance will be collected up to this date. Data on HRQoL and satisfaction will be subjected to analysis for all patients enrolled up to July 31, 2024, in order to be able to map the development over half a year (from t0 to t1).

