### Data collection and management

#### Plans for assessment and collection of outcomes

##### Patient satisfaction and HRQoL

The participating patients are administered the SF- 12, a questionnaire frequently used in clinical studies, to assess their HRQoL. Additionally, the ZUF- 8, a questionnaire designed to assess patient satisfaction, is used after being adapted to the context of the “home visit” or “VaO” setting. Both questionnaires are completed at three points in time (t0 before the first VaO room visit of the patient, t1 after six months, t2 after 12 months) during the course of the study to observe and evaluate changes.

In addition, focus group interviews will be conducted with the participating HPs on their satisfaction with VaO concept at survey times t1 and t2. Therefore, we designed an interview guideline which covers important objects like time saving or the changes due to the use of VaO in everyday working life (Appendix A). The interviews are intended to capture the range of opinions of the HPs regarding the innovative VaO concept in an open discussion to validate or question its components. Additionally, potential success factors or barriers to the implementation of the concept will be identified.

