### Statistical methods

#### Statistical methods for primary and secondary outcomes

Table 1 shows the statistical methods used to analyse quantitative data.

**Table 1 Tab1:** Statistical methods used for quantitative data sets

Data	Points in time	Statistical method
SF- 12	t0, t1, t2	Descriptive statistics, paired t test, ANOVA with repeated measures
ZUF- 8	t0, t1, t2	Descriptive statistics, paired t test, ANOVA with repeated measures
Kilometers	continuous	Descriptive statistics, paired t test, Wilcoxon test
Time	continuous	Descriptive statistics, paired t test, Wilcoxon test

The baseline data (t0) on HRQoL and patient satisfaction are analysed using descriptive statistics. To assess the changes that occurred after the first survey and testing phase, data collected at t0 and t1 are compared using paired t-tests or Wilcoxon test as part of an interim analysis. Upon completion of the second survey and testing phase, all data from the three measurement points (t0, t1 and t2) are subjected to a repeated measures ANOVA to compare outcomes across all three time points.

Additionally, the distance travelled and time spent are compared between the VaO scenario and the home visit scenario. Given the conditions shown, paired t tests or Wilcoxon test are used to determine whether there are any discernible differences in the parameters under examination.

The emphasis is on understanding underlying trends, patterns and on gaining real world evidence.

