### Trial status

Version 1, status 31/03/2023. Recruitment began at 22/05/2023 and is still ongoing until 31/12/2024. Trial was registered at the German Clinical Trials Register (DRKS00033915) – Registration Date 19/03/2024.

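### The 31 July 2024 cut-off for HRQoL and satisfaction fits the six-month visit only: patients enrolled after 30 June 2024 reach the 12-month t2 after the study ends

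*Protocol article*

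**What the plan says.** Four statements in the protocol article bear on this.

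- **Patient recruitment.** HRQoL and satisfaction data undergo "analysis for all patients enrolled up to July 31, 2024, in order to be able to map the development over half a year". The interval named is t0 to t1; t2 is not mentioned. For enrolment as such, "The final date for patient enrolment is December 31, 2024".
- **Patient satisfaction and HRQoL.** Questionnaires are timed per patient: "t0 before the first VaO room visit of the patient, t1 after six months, t2 after 12 months". The Outcomes section and the Discussion also give six and 12 months.
- **Trial design.** "It is conducted from January 2023 to June 2025, spanning a total duration of 30 months". The final evaluation, which tests the hypotheses, comes at the end of that period.
- **Statistical methods for primary and secondary outcomes.** t0 and t1 are compared in an interim analysis by paired t test or Wilcoxon test. After the second survey phase, "all data from the three measurement points (t0, t1 and t2) are subjected to a repeated measures ANOVA".

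The Sample size section matches the last of these: one group, three time points, effect size 0.25, correlation 0.5, nonsphericity correction 1, giving 28 patients and power 0.81. It mentions no allowance for missing measurements.

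**The concern.** The cut-off decides who belongs to the HRQoL and satisfaction analysis, and its only stated reason is the six-month interval. The analysis that uses all the questionnaires needs the 12-month value too. Some patients admitted by the cut-off therefore cannot have a t2 within the study period, however well follow-up is run. A classical repeated measures ANOVA needs all three values and drops them.

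Two things are at stake. First, the number of patients in the three-time-point test may fall below the number it was sized for. Hypotheses 3 and 4 expect no change, so lost power makes a non-significant result more likely and could be mistaken for support. Second, changes to t1 and to t2 would describe different groups of patients, and both enter the benefit term of the ICER in the Costs section.

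**Working it through.** **Inputs.** Recruitment start 22 May 2023 (Trial status); analysis cut-off 31 July 2024 and last enrolment 31 December 2024 (Patient recruitment); study end June 2025, read at its latest as 30 June 2025 (Trial design); t1 at six and t2 at 12 months (Patient satisfaction and HRQoL); f = 0.25, alpha = 0.05, m = 3 measurements, correlation 0.5, nonsphericity correction 1 (Sample size).

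**Assumptions not in the article.** Enrolment is uniform over time, exactly 28 patients are enrolled by the cut-off, and t0 falls on the enrolment date. If the first VaO room visit comes later than enrolment, t2 moves later too.

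**Step 1: the plan's own figure.** For the within-subject F test, the noncentrality is lambda = f² × N × m / (1 − correlation), with df1 = m − 1 and df2 = (N − 1)(m − 1). At N = 28, lambda = 0.0625 × 28 × 3 / 0.5 = 10.5 with 2 and 54 df, and power is 0.8125. At N = 27 power is 0.796, so 28 is the smallest adequate number. The stated 28 and 0.81 reproduce.

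**Step 2: dates for the last admitted patient.** 31 July 2024 plus six months is 31 January 2025, inside the study. Plus 12 months is 31 July 2025, a month after the latest possible end. The last enrolment date that allows t2 by 30 June 2025 is 30 June 2024.

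**Step 3: share without t2.** From 22 May 2023 to 31 July 2024 is 437 days, counting both ends. The enrolment days too late for t2 are counted back from 31 July 2024. Power is computed as in Step 1, with N equal to the number complete.

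| Last questionnaire | Latest enrolment for t2 | Share without t2 | Complete of 28 | Power |
|---|---|---|---|---|
| 30 June 2025 | 30 June 2024 | 31/437 = 7% | 28 × 406/437 ≈ 26 | 0.78 |
| 31 March 2025 | 31 March 2024 | 122/437 = 28% | 28 × 315/437 ≈ 20 | 0.65 |
| 31 January 2025 | 31 January 2024 | 182/437 = 42% | 28 × 255/437 ≈ 16 | 0.54 |

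Only the first row uses a date the article gives. The others show how the loss grows if collection stops earlier to leave time for the final evaluation.

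**Step 4: enrolment that would offset the minimum loss.** 28 / (406/437) = 30.1, so 31 enrolees by the cut-off.

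**Step 5: the other side of the cut-off.** Patients enrolled from August to December 2024 (153 of 590 enrolment days, 26%) have t1 due between February and the end of June 2025. All of these t1 values can be collected only if questionnaires run to 30 June 2025. With closing on 31 March 2025, only those enrolled in August and September (61 of 590 days, 10%) have a t1 in time. With closing on 31 January 2025, none do. So the t2 loss is largest when nothing usable is discarded, and smallest when most is.

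**The case against.** Several points on the other side stand.

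- **Size.** The only loss tied to a stated date is that of the July 2024 enrolees, 7%. A reader might infer that questionnaires close on 31 January 2025, because the last admitted patient's t1 falls due then, and so expect a 42% loss. The article does not say that collection stops on that date. The survey calendar may be in Fig. 1, which was not available for this check.
- **Both harms at once.** It is tempting to put the 42% loss of t2 beside the 26% of enrolment days excluded. By Step 5 the two cannot hold together.
- **Sample size.** It would be wrong to say that 28 and 0.81 do not apply. They hold for 28 patients with all three measurements. The falls in power assume exactly 28 enrolled by the cut-off, a number the article does not give.
- **Openness.** The article says plainly that the cut-off serves t0 to t1 and plans a separate t0-t1 comparison. Excluding later enrolees also has a practical reason: a patient enrolled on 31 December 2024 reaches t1 at the very end of the study.
- **Analysis plan.** How incomplete patients are handled can be left to an SAP. But an SAP cannot bring t2 forward, and both the cut-off and the ANOVA are fixed here.

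One could also note that the Abstract places t1 and t2 after study phases. If t2 were phase-based, late enrolees could have one, but not at 12 months as three other sections state.

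**Conclusion.** The dates conflict. The cut-off admits patients who cannot have a 12-month value before the study ends, and the planned final analysis requires that value. This follows from stated dates under every reading of the June 2025 end.

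The minimum size is modest: 7% without t2, about 26 of 28 complete, power 0.78 instead of 0.81, given uniform accrual and 28 enrolees. Enrolling about 31 would remove it. Larger losses depend on a closing date that the article does not state. The loss of usable t1 data after 31 July 2024 is likewise conditional, on questionnaires running past January 2025.

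A reader might conclude that the study's main result is in danger. The article does not support that: travel and setup time are the primary outcomes, they are collected up to 31 December 2024, and this cut-off does not touch them. HRQoL and satisfaction are secondary, so the point should be fixed but is not critical.

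**What to change.** Reconcile the cut-off with t2 and the study end:

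1. State the last date on which a questionnaire can be collected.
2. Define the t0-t1-t2 set as patients enrolled at least 12 months before that date, and the t0-t1 set as patients enrolled at least six months before it. Where t0 falls after enrolment, count from t0.
3. Replace the complete-case ANOVA by one linear mixed model with time as a categorical effect, using every available questionnaire and reporting the t0-t1 and t0-t2 changes. Because t2 is then missing by enrolment date, say that change is assumed not to depend on when a patient enrolled.
4. State that 28 and 0.81 refer to patients with all three measurements, and report how many there are.

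The minimum version is one sentence saying which enrolees contribute to t0-t1 only and which to the three-time-point analysis. The full version costs some wording and one model in place of another, and needs no new patients. The downside is that the t2 result may be stated for a smaller number, and data entry may run slightly later.

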### Eligibility criteria

We defined eligibility criteria for all participating groups: GPs, HPs and patients. First, GPs qualify for participation if they are established in the Streutal region. Second, HPs qualify if they are employed by a participating GP and care for home visit patients. Third, patients qualify for participation if they are selected by the participating GPs based on the following defined inclusion criteria:

Patient is treated by a participating GP.Patient receives home visits from a HP that is employed by a participating GP.Patient provides voluntary and written consent for pseudonymized recording of HRQoL and satisfaction as well as processing to and analysing by the evaluating team.Patient provides voluntary and written consent for anonymised recording of the care provided and the structural data (distance and time) of the home visit route as well as processing to and analysing by the evaluating team.Patient is capable of visiting the VaO room (according to the assessment of the GP in charge).Patient is 18 years of age or older.Patient has sufficient knowledge of German.

The patients participating in the study provide written informed consent to their GPs after being informed of the details of the study and their participation, particularly the associated change in their care (the establishment of the VaO room, where basic treatment sequences may be conducted by the HPs). They are also informed of their voluntariness and the right to withdraw at any time, which entails a change to the previous way of care through home visits.

### Intervention description

After being selected by the participating GPs and providing informed consent, patients receive their medical care through delegated services in one of the established VaO rooms during all phases of the study as long as they meet the inclusion criteria. They receive the same care as if they were at home – the range of services provided by HPs is not extended, only the location of the service changes. For instance, services such as the collection of blood samples, the measurement of blood sugar levels or the treatment of wounds may be provided at the VaO rooms. The HP-patient relationship remains the same as well, as the HPs continue to see the same patients they have seen in their home visits.

The use of the VaO rooms is organised independently of the practices. This means that presence times and patient timing are managed by the HPs themselves so that the VaO rooms can be individually integrated into practices’ daily routine. For example, the frequency of opening the VaO room or the type of patient appointment can be determined by the practices. This concept is based on continuity, as the combination of GP, HP, patients and services remains unchanged. This makes it possible to change the location of care provision without interfaces and without loss of any information.

### Outcomes

The primary outcomes include time saved in the nonpatient area: travel and setup time. Based on the patients who are cared for and the services that are given in the VaO rooms (VaO scenario), the amount of travel and setup time can be analysed and compared to the time that would have been needed if services were given in the original home visiting route (home visit scenario).

Two secondary outcomes are considered. First, patients’ HRQoL is assessed using the SF- 12 questionnaire which is based on a physical and psychological summated scale. The standardised and validated questionnaire is used because it is known to be simple and quick to administer in the assessment of HRQoL. As a generic measurement instrument for self-reported HRQoL it is particularly suitable for the target group, as it consists of older patients who are asked to make independent statements about their health [17]. The questionnaire is comparatively easy to use as it consists of only 12 items [18]. Second, patient satisfaction is measured using the ZUF- 8 instrument, which is a standardised tool for measuring satisfaction in an inpatient context. It was selected on the basis of its multiple uses in studies and appropriate evaluation of the quality criteria [17, 19]. To examine the changes in HRQoL and patient satisfaction, these parameters are surveyed at three time points during the study, as shown in Fig. 1 (time points t0 as baseline, t1 after six months as midterm, and t2 after 12 months as final examination).

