## Objectives

The overall aim is to (1) implement the VaO concept in a real-world setting in the Streutal Valley in Northern Bavaria and to (2) evaluate its effectiveness by assessing economic efficiency, satisfaction and HRQoL in compared to the usual care provision.

Therefore, the primary objective is to conduct a health economic evaluation of VaO as a minor modification and resource-saving interdisciplinary form of care to mitigate the shortage of GPs in rural areas. The secondary objective is to test its feasibility and integration into the daily routines of patients, HPs and GPs as well as to evaluate the psychosocial effects of the concept. The following hypotheses are being tested to answer the selected research question.

Hypothesis 1: The monetary expenses and savings of the VaO care model lead to economically neutral to positive results for the GPs running the rooms.Hypothesis 2: The VaO care model reduces average working time spent in nonpatient areas (travel and setup time).Hypothesis 3: The VaO concept does not lead to a change in patients’ HRQoL.Hypothesis 4: The VaO concept does not lead to a change in patients’ and HPs satisfaction.

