### Sample size

As the study initially pursues the general proof of concept and has an observational character, it aims to explore complex interactions and the evolution of the use of VaO rooms rather than to quantify specific instances. We see the development of the usage of the VaO rooms, the number of patients receiving care and the given services as indicators of study success. The sample size estimation is conducted using the tool G*Power Version 3.1.9.7 of Heinrich Heine University of Düsseldorf. The calculation is based on an expected effect size of 0.25, an alpha error level of 0.05 and a statistical power of 0.80. Given the repeated measures ANOVA design, the number of groups is set to one with three measurement time points. Additionally, a correlation of 0.5 between repeated measures is assumed, and the nonsphericity correction is set to the default value of one. This results in a required total sample size of 28, with an actual power of 0.81.

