##### Costs

The costs of the innovative form of care are calculated using the existing remuneration models for medical assistants in job group IV of the German Collective Labour Agreement for Medical Assistants. The average salary and the average monthly working time of a full-time HP are calculated using the collective agreement for medical assistants of the Bavarian Medical Association [21, 22]. The exact values are one basis for calculating the expected cost savings from VaO.

To measure the cost-effectiveness of the intervention, the incremental cost-effectiveness ratio (ICER) of the innovative care system VaO in comparison to the standard method of care is calculated. Mathematically, the ICER sets the difference in costs in relation to the difference in benefits and allows to illustrate the drivers and limitations (e.g., effects of VaO room utilisation, logistical challenges) of cost-effectiveness:

$$\mathrm{ICER}\;=\;({\mathrm C}_{\mathrm{VaO}}-{\mathrm C}_{\mathrm{standard}})/({\mathrm B}_{\mathrm{VaO}}-{\mathrm B}_{\mathrm{standard}})$$

C_VaO_ includes the calculated costs of the care system VaO, namely, room rent (including maintenance and cleaning), which is calculated from the local standard comparative rent, as well as the costs of travel distances and times according to the VaO route planning when using the VaO rooms.

C_standard_ includes the cost of travel distances and times according to standard route planning.

B_VaO_ includes the benefit expressing change in satisfaction and HRQoL from t0 to t1 and t2 as mentioned above as a reflection of the satisfaction with the innovative form of care.

B_standard_ includes the benefit expressing average HP and patient satisfaction at time t0, reflecting satisfaction with their usual form of care.

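### The primary objective is economic, but the only primary outcome named is time saved, which cannot register the room costs that the plan charges to VaO alone

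*Protocol article*

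**What the plan says.** All references are to the protocol article.

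- **Objectives.** The text states that "the primary objective is to conduct a health economic evaluation of VaO as a minor modification". Hypothesis 1 reads: "The monetary expenses and savings of the VaO care model lead to economically neutral to positive results for the GPs running the rooms". Less working time away from patients is a separate Hypothesis 2. Hypotheses 3 and 4 expect no change in HRQoL or in satisfaction.
- **Outcomes.** "The primary outcomes include time saved in the nonpatient area: travel and setup time". The section continues: "Two secondary outcomes are considered", and these are the SF-12 and the ZUF-8. No cost or net monetary result is named at either level.
- **Costs.** The VaO cost term contains "room rent (including maintenance and cleaning), which is calculated from the local standard comparative rent", plus travel distance and time on the VaO routes. The standard-care term "includes the cost of travel distances and times according to standard route planning". The one statistic named is an ICER whose benefit side is satisfaction and HRQoL.
- **Time and distance savings.** Setup times were measured separately with the HPs and enter the evaluation of time savings.
- **Sample size.** The development of room usage is named together with "the number of patients receiving care and the given services as indicators of study success".

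**The concern.** The primary outcome should answer the primary objective. Here the objective and Hypothesis 1 concern money, while the declared primary outcome concerns hours. Hours saved are one input to the money result, on the savings side. The main new expense, the room, is on the other side and never enters the outcome.

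The headline is at stake. A report that leads with its declared primary outcome could show a clear time saving and read as a success while the practices paying for the rooms lose money. The result that would show this is planned only as an ingredient of a ratio.

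**Working it through.** **1. The plan's own figure.** The only calculated figure is the sample size. For a one-group repeated measures ANOVA with f = 0.25, three time points, correlation 0.5 and N = 28, the noncentrality is 0.25² × 28 × 3 / (1 − 0.5) = 10.5 on 2 and 54 degrees of freedom. Power is 0.8125, and N = 27 gives 0.796, so the stated 28 and 0.81 reproduce. The Statistical methods section assigns this ANOVA to the SF-12 and ZUF-8. The figure therefore bears on neither time saved nor the economic result.

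**2. What each quantity contains.**

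| Component | Time saved (primary outcome) | C_VaO | C_standard |
|---|---|---|---|
| Travel time | yes | yes | yes |
| Setup time | yes | not named | not named |
| Distance | no | yes | yes |
| Rent, maintenance, cleaning | no | yes | no |

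Two things follow. Time saved omits a cost that falls on one scenario only. The cost terms, whose times are those of the route planning, omit setup time, although it is part of the primary outcome.

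**3. Can time saved and the net result differ in sign?** Counting labour only, net result per room-month = hours saved × hourly labour cost − room cost. The documents give no rent or wage, so these inputs are assumptions: room cost EUR 100 to 500 per room-month, labour EUR 20 to 30 per hour.

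- Break-even hours = room cost / hourly cost: from 100/30 = 3.3 to 500/20 = 25 per room-month. Over the seven rooms this is 23.3 to 175 hours per month.
- At EUR 300 and EUR 25 per hour, break-even is 300/25 = 12 hours. Saving 8 hours gives 8 × 25 − 300 = −EUR 100. Saving 16 hours gives 16 × 25 − 300 = +EUR 100.

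Crediting kilometres as well, at an assumed EUR 0.30 per km, 30 to 40 km/h and EUR 20 to 25 per hour, one driving hour saved is worth 20 + 0.30 × 30 = EUR 29 to 25 + 0.30 × 40 = EUR 37. With an assumed room cost of EUR 150 to 450, break-even is 150/37 = 4.1 to 450/29 = 15.5 hours per room-month.

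Both 8 and 16 hours count as time saved, yet the sign of the net result changes between them.

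**4. Does the ICER show break-even?** ICER = (C_VaO − C_standard) / (B_VaO − B_standard).

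- An extra cost of EUR 100 with a gain of 1 point gives 100/1 = 100. A saving of EUR 100 with a loss of 1 point gives (−100)/(−1) = 100. A loss and a gain for the practice yield the same ratio.
- If Hypotheses 3 and 4 hold, an incremental benefit is near zero. With an extra cost of EUR 100, a difference of +0.1 gives 1,000 and −0.1 gives −1,000. The ratio is unstable when the concept works as intended.
- This reads the denominator as an incremental benefit. The Costs section words B_VaO as a change and B_standard as a level at t0. Taken literally that is not a benefit difference, and it shows break-even no better.

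**The case against.** The best defence is that the Costs section already holds the needed quantity. C_standard minus C_VaO is travel savings minus room costs, and its sign tells whether VaO saves money. The section also mentions expected cost savings apart from the ratio, and the Trial design section says that the final evaluation tests the hypotheses. Hypotheses 1 and 2 are stated separately, so different answers to them are no contradiction. The verb used for the primary outcomes leaves the list open.

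Much of this stands, and it rules out several stronger readings:

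- **Hypothesis 1 has no measure or goes unanswered.** A reader might infer this, but the cost components are defined and the hypothesis can be addressed.
- **The missing cost row in Table 1, or the missing tolerance for a neutral result, is a defect.** Table 1 lists tests for collected data, whereas costs are derived from them. A tolerance is detail that a condensed article may leave to the full protocol or analysis plan.
- **Room usage is a rival endpoint.** The Sample size section uses it as descriptive proof-of-concept language without a threshold.
- **VaO is likely to lose money.** Every price above is assumed. With enough hours saved, every case shows a gain.

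The defence does not remove the mismatch. An open list that names no economic outcome still leaves the primary objective without a declared one. A numerator that is never declared as a result, and that omits setup time, is not yet the answer to Hypothesis 1.

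**Conclusion.** The point holds as an alignment fault. The declared primary outcome belongs to Hypothesis 2, while the primary objective and Hypothesis 1 call for a net monetary result. The plan can compute most of that result, but it neither declares it nor costs setup time in it, and it names only a ratio unsuited to the question.

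The documents do not fix the size in money. Under the assumed prices, break-even lies between 3.3 and 25 hours saved per room-month, so a favourable time result with a net loss is possible. That conclusion needs only that room costs fall on VaO alone, which the Costs section states. How likely a loss is cannot be judged from the documents. The change is worth making because it is cheap and lets the study answer its own primary question.

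**What to change.** - **Outcomes:** name the net monetary result for the GPs running the rooms, C_standard minus C_VaO, as the primary outcome for Hypothesis 1. Keep time saved as the outcome for Hypothesis 2 and as an input.
- **Costs:** include setup time in both cost terms, using the same setup times as the time-saved outcome.
- **Reporting:** give the net result in total and per practice, with a sensitivity range over rent, wage and room use, and state the break-even room use. A confidence interval per room is poorly suited here, because three practices share the rooms, routes are modelled and rent is calculated.
- **Judging Hypothesis 1:** base it on this net result and not on the ICER.
- **Sample size:** state that room usage, patient numbers and services are descriptive feasibility indicators.

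The cost is a few sentences and a small extra analysis, built mainly on inputs already planned under Costs and under Time and distance savings. The headline may be less favourable than time saved alone.
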